# Effectiveness and safety of acupoint catgut embedding for patients with mild psoriasis and overweight: study protocol of a multicenter double-blind randomized controlled trial

**DOI:** 10.3389/fmed.2026.1796602

**Published:** 2026-03-19

**Keywords:** acupoint catgut embedding, comorbidity, obesity, overweight, perineal trauma, psoriasis

## Abstract

**Background:**

Psoriasis is a systemic inflammatory disease frequently comorbid with obesity, as both conditions share common pathogenic pathways. Acupoint catgut embedding (ACE), a sustained-release form of acupuncture, has demonstrated potential in modulating both immune and metabolic responses. This trial aims to evaluate the efficacy, safety, and underlying mechanisms of ACE in patients with mild psoriasis and concurrent overweight/obesity.

**Methods:**

This is a multicenter, randomized, double-blind, sham-controlled trial. Participants aged ≥ 18 years with mild plaque psoriasis (PASI< 3, BSA < 3%) and overweight (BMI ≥ 24 kg/m^2^) will be randomized (1:1) to receive either verum ACE at 14 specific acupoints or a sham procedure. Interventions will be administered every 2 weeks for 8 weeks. The primary endpoints are the changes in PASI score and BMI from baseline to week 8. Secondary outcomes include the Dermatology Life Quality Index (DLQI), waist circumference (WC), lipid profiles, and systemic inflammatory markers. The safety of the procedure will be monitored through the recording of adverse events and conducting laboratory tests. Participants will be followed through week 32 to evaluate long-term therapeutic durability.

**Discussion:**

This trial will provide high-quality evidence regarding the “dual-action” potential of ACE in simultaneously improving psoriatic lesions and metabolic dysfunction, establishing its role as an integrative therapy for this specific patient phenotype.

**Clinical trial registration:**

https://itmctr.ccebtcm.org.cn/, identifier ITMCTR2025002460.

## Introduction

1

Psoriasis is a chronic, immune-mediated inflammatory skin disorder driven by a complex interplay of genetic and environmental factors. Beyond its cutaneous manifestations, psoriasis is increasingly recognized as a systemic disease, frequently co-occurring with metabolic syndrome (MetS) in 20 to 50% of patients (1, 2). Key components of MetS—including obesity, dyslipidemia, and impaired glucose metabolism—are not merely comorbidities but are fundamentally linked to the disease’s severity (3–5). Evidence shows that the Psoriasis Area, Severity Index (PASI) scores positively correlate with body weight, cholesterol levels, and glycemic markers (6). Crucially, these metabolic abnormalities often persist after skin clearance, acting as long-term prognostic markers that can trigger future relapses (7, 8).

Central to this systemic interplay is obesity, which serves as a potent aggravating factor for psoriatic inflammation. Adipose tissue in obese individuals acts as an active endocrine organ, secreting pro-inflammatory cytokines such as leptin, IL-6, and TNF-*α*, while directly fuel the Th17/IL-17/IL-23 axis—the primary driver of psoriatic lesions (9–13). This creates a self-perpetuating “psoriatic-metabolic” inflammatory loop. While clinical evidence underscores that weight loss can significantly improve psoriasis outcomes (14, 15), standard systemic treatments often fail to address this metabolic driver. For instance, while biologics offer rapid skin clearance, their impact on metabolic parameters like BMI and insulin resistance remains inconsistent and lacks confirmation from large-scale prospective trials (16).

To bridge this therapeutic gap, Acupoint Catgut Embedding (ACE), emerges as a promising integrative strategy. As a sustained-release form of acupuncture, ACE involves embedding absorbable sutures into specific acupoints to provide continuous stimulation (17–22). By embedding absorbable catgut sutures at specific acupoints, ACE provides continuous and sustained stimulation to elicit therapeutic responses, thereby achieving long-lasting effects (23). Years of research have confirmed its efficacy and safety. In particular, the application of ACE for the treatment of obesity is supported by extensive clinical observations and mechanistic studies (24). Li et al. found that ACE can improve body composition, including reductions in body mass index (BMI) and waist-to-hip ratio (WHR) through appetite regulation, while also ameliorating metabolic parameters such as blood lipid and glucose levels (25–28). More importantly, its mechanism closely with the needs of psoriatic patients: ACE modulates chronic low-grade inflammation by downregulating IL-6, TNF-*α*, and MCP-1, while simultaneously ameliorating leptin resistance and enhancing insulin sensitivity (29, 30).

Despite its therapeutic potential, the clinical adoption of ACE for psoriasis remains hindered by a lack of high-quality evidence. Current research is predominantly limited to small-scale case series or trials with methodological inconsistencies. There is an urgent need for robust, multicenter randomized controlled trials (RCTs) to definitively establish the efficacy and safety of ACE in this specific patient population and to elucidate its underlying biological mechanisms.

This multicenter, double-blind, randomized controlled trial aims to evaluate the efficacy of ACE compared to a sham procedure in patients with mild psoriasis and overweight/obesity. We hypothesize that ACE will demonstrate superior efficacy in reducing both psoriasis severity and metabolic dysfunction, providing a novel integrative strategy for this specific patient phenotype.

## Methods and design

2

### Study setting and recruitment

2.1

This multicenter double-blind randomized controlled trial employs a two-arm, 1:1 allocation design. Conducted from January 2026 to December 2027, the study will recruit participants primarily from the dermatology outpatient clinics of two tertiary hospitals—the Second Affiliated Hospital of Hunan University of Chinese Medicine and Xiangya Hospital, Central South University, both are tertiary hospitals, supplemented by community-based recruitment (like publishing recruitment advertisements through online platforms). The trial procedure is summarized in Figure 1. The study protocol was developed in accordance with the Interventional Trials (SPIRIT) guidelines (31) and STRICTA guidelines (32).

**Figure 1 fig1:**
[figure not shown]
Flow diagram of the study design.

### Randomization and blinding

2.2

Participants will be randomly assigned to either the verum ACE group or the sham ACE group in a 1:1. A computer-based central randomization system, managed by an independent statistician not involved in patient recruitment or intervention, will be used to generate the allocation sequence (33).

Participants, data collectors, data analysts, and recruiting physicians will be blinded to group allocation. To ensure blinding, the recruitment physician will be responsible for screening potential participants, obtaining informed consent, and completing the randomization procedure, but will have no further involvement in the trial. Following randomization, operators will use delivery devices pre-loaded according to the allocation codes, such that the presence or absence of the absorbable suture remains concealed. Except for the actual embedding of the catgut, all procedural steps—acupoint localization, skin disinfection, and needling technique—will be strictly standardized across both groups to minimize performance bias (34–37). Data collectors, who will assess clinical outcomes, and the statistician performing the final analysis will be also blinded to group allocation. This multi-tiered blinding strategy ensure that only the third-party researcher preparing the kits is aware of the allocation sequence. At trial completion, a blinding assessment will be conducted among participants and practitioners, and the accuracy of their group guesses will be tested against the 50% chance level using a chi-square test. This rigorous design ensures that treating physicians, data collectors, statisticians, operators, and patients remain blinded throughout the study. The trial is registered with the International Traditional Medicine Clinical Trial Registration Platform (Registration No. ITMCTR2025002460).

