### Sample size calculations

2.11

Based on our pilot data, the verum ACE achieved an improvement rate of 60%. Since no sham-controlled acupuncture trials for psoriasis are available, we derived the sham group response rate from the placebo effect observed in psoriasis pharmacological trials, which was approximately 25% as reported in the literature (40). Sample size estimation was performed using the standard formula for comparing two independent proportions (two-sided test, *α* = 0.05, power = 80%):

$$n1=n2=\frac{{\left(Z_{1-\alpha /2}+Z_{1-\beta }\right)}^{2}\times [p_{1}(1-p_{1})+p_{2}(1-p_{2})]}{{\left(p_{1}-p_{2}\right)}^{2}}$$

Where p_1_ = 0.60, p_2_ = 0.25, Z_1 − α/2_ = 1.96, and Z_1 − β_ = 0.84. The calculated sample size was 28 participants per group. After adjusting for a 20% dropout rate, the final sample size was determined to be 35 participants per group (total 70 participants).

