### Intervention

2.12

All participants will receive standardized baseline care. For skin lesions and xerosis, urea vitamin E cream (Fuyuan Pharmaceutical Co., Ltd., National Medicine Permit No. H34022160) will be applied as a moisturizer. Additionally, all patients will undergo health education regarding lifestyle and dietary modifications, along with training in daily skin care. To enhance adherence and objectively monitor compliance, researchers will add all participants to a WeChat health management group.

Participants will be instructed to photograph their daily meals; the images will be analyzed via a dedicated mobile application to estimate caloric intake. Daily step counts will be automatically recorded and tracked through the WeChat sports mini-program.

Throughout the trial, participants may continue their usual medications for comorbidities (e.g., diabetes, hyperlipidemia). We will require them to maintain the same types and doses of their underlying disease medications during the trial, with any changes in medication recorded at each visit. However, the use of any treatments specifically targeting psoriasis is prohibited.

(1) Experimental group:

In addition to conventional care, patients in the verum group will receive true catgut embedding acupuncture (needle insertion followed by thread embedding), at the following points: CV12 (Zhongwan), CV4 (Guanyuan), SP15 (Daheng), ST25 (Tianshu), ST36 (Zusanli), BL20 (Pishu), BL18 (Ganshu), and SP10 (Xuehai). All points are needled bilaterally except for CV 12 and CV 4. These acupoints were selected based on a comprehensive review of prior literature and established clinical expertise. This combination is designed to simultaneously address psoriatic inflammation and underlying metabolic dysfunction. Previous studies suggest that points such as ST25 (Tianshu), SP15 (Daheng), CV12 (Zhongwan), ST36 (Zusanli), and BL20 (Pishu) can help improve central obesity and gastrointestinal function (41, 42), while SP10 (Xuehai) is traditionally used to activate blood circulation and resolve stasis, and BL18 (Ganshu) is employed to promote blood circulation and regulate qi.

The acupoints were localized according to the World Health Organization Standard Acupuncture Point Locations. All acupuncture point locations are shown in Figure 2.

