Complete blood count, liver function, and renal function: laboratory tests including complete blood count, liver function, and renal function were ordered by physicians and performed by the hospital laboratory.

(1) *ECG*: ECG was ordered by physicians and performed by the hospital ECG department.(2) *AEs*: AEs were reported by study participants during the intervention and follow-up periods, regardless of their relationship to the study intervention.

All data collection time points are shown in Tables 1, 2.

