### Harms

2.22

During the study, local pain, swelling, distension, and itching may occur at the acupoint embedding sites, and adverse changes such as decreased appetite, diarrhea, and constipation may also occur (56–59).

To reduce these injuries, we will strictly screen participants before enrollment. If relevant symptoms already appear, we will systematically assess their severity: (1) If there is local redness and pain, no special treatment is required; keep the area dry, and if the pain is significant, cold compresses can be applied. (2) If local subcutaneous bleeding occurs, apply a cold compress to stop the bleeding, followed by warm compresses to promote bruise absorption. (3) If sutures are expelled, disinfect with iodine solution and avoid pulling them out by yourself; if accompanied by redness and swelling, medical treatment is required. (4) If local induration occurs, it often resolves on its own after surgery; if the induration continues to enlarge, medical treatment is necessary. (5) If allergic reactions or shock should occur, stop the experiment immediately and seek medical treatment as appropriate.

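### Blinding of the PASI raters and participants is not secured against signs that only an embedded suture can produce

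*Protocol article*

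**What the plan says.** All references are to the protocol article.

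- **The claim.** Section 2.2: "Data collectors, who will assess clinical outcomes, and the statistician performing the final analysis will be also blinded to group allocation". The same section concludes that operators, data collectors, statisticians and patients all stay blinded to the end. Section 2.3 describes the sham as matching the real procedure in everything visible or felt.
- **The difference between arms.** Under Section 2.13 the same needle enters muscle in both arms, and only the suture is left out of the sham.
- **Foreseen reactions.** Section 2.22 gives instructions for several local reactions, among them: "If sutures are expelled, disinfect with iodine solution and avoid pulling them out by yourself". It also mentions local induration, without tying it to an arm.
- **Who scores and when.** Section 2.17 has two trained investigators score PASI and BSA separately, with the results averaged. Tables 1 and 2 mark both PASI and adverse events at weeks 4, 8, 12, 16, 24 and 32.
- **Adverse-event reporting.** Section 2.17: "AEs were reported by study participants during the intervention and follow-up periods". Section 2.14 has participants report discomfort to a coordinator.
- **Contact between participants.** Section 2.12: "researchers will add all participants to a WeChat health management group", for adherence and compliance monitoring.
- **Checking the blind.** Section 2.2 plans a guess-the-arm check at the end of the trial among participants and practitioners. Outcome raters are not included.
- **Limitations.** Section 4 concedes possible operator bias and a different physical stimulus. It mentions neither the raters nor the chat group.

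**The concern.** PASI is a co-primary endpoint and, like BSA and PGA, a rater's judgement. DLQI and itch are self-reports, and DLQI is completed with an investigator's guidance. A sign confined to the verum arm unmasks that arm selectively. If it influences scoring, the likely direction is in favour of verum.

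The article leaves two routes open. A rater may see the sign on the skin or hear of it at the visit. A participant may see it, or learn in the shared group what a real embedding looks like; sham participants without such a sign may then suspect their own assignment. The planned check comes too late to prevent either, and it cannot detect unmasked raters because they are not asked.

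**Working it through.** **1. The only related figure in the plan.** The article gives no number on blinding. Its sample size reproduces (Section 2.11: 60% against 25%, two-sided α 0.05, 80% power):

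(1.96 + 0.84)² × [0.60 × 0.40 + 0.25 × 0.75] / 0.35² = 7.84 × 0.4275 / 0.1225 = 27.36, rounded up to 28. This agrees with "The calculated sample size was 28 participants per group". With 20% dropout, 28 / 0.80 = 35. Nothing below changes it.

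**2. Statements side by side.**

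| Claim | Fact elsewhere in the article |
|---|---|
| Sham matches in everything visible (2.3) | Expelled sutures are planned for (2.22); sham has none to expel |
| Assessors stay blinded (2.2) | PASI and adverse events share six visits (Tables 1, 2); treated points lie on abdomen, back, thigh and leg (2.12); no separation of rater and recorder at visits is stated |
| Patients stay blinded (2.2) | Both arms are in one chat group (2.12) |
| Blinding will be assessed (2.2) | Raters are not asked |

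**3. Exposure.** Six bilateral points plus two midline points make 14 per session. Over four sessions (2.13) that is 14 × 4 = 56 sutures per verum participant and none per sham participant. The rate q of visible suture-only reactions per suture is not given. I assume 0.05% to 2%, independent between sutures.

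Share of verum participants with at least one: 1 − (1 − q)^56. Chance of at least one case among 35: 1 − (1 − q)^(56 × 35).

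| q | Share of verum | Expected of 35 | At least one among 35 |
|---|---|---|---|
| 0.05% | 2.8% | 1.0 | 62% |
| 0.1% | 5.4% | 1.9 | 86% |
| 0.5% | 24.5% | 8.6 | over 99% |
| 1% | 43.0% | 15.1 | over 99% |
| 2% | 67.7% | 23.7 | over 99% |

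The last column matters for the chat group, where one report could reach everyone.

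**4. Effect on the PASI comparison, no true difference, 35 per arm.**

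*Responder version*, on the scale of the sample-size calculation: true response 25% in both arms; in the unmasked share of verum, the probability of being scored a responder rises by 10 to 35 percentage points. Exact enumeration of the two-sided pooled z test.

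*Continuous version*, closer to the planned mixed model: unmasked participants are scored 0.25 to 1.0 SD better, so the mean bias is share × shift; standard error √(2/35) SD, normal approximation.

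| Share unmasked | False-positive rate, responder | False-positive rate, continuous |
|---|---|---|
| 0% | 4.8% | 5.0% |
| 10% | 4.9–6.1% | 5.1–7.0% |
| 25% | 5.5–12.6% | 5.8–18.2% |
| 50% | 7.4–34.8% | 8.2–55.2% |

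The shares and shifts are assumptions. The document gives nothing to choose between the rows.

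**The case against.** **The article is condensed.** Visit order, who records adverse events, and rules for the chat group may be in the full protocol, which Section 2.23 says is a supplement and which is not shown. This stands against reading silence as a defect. It does not remove what is stated. Separating the roles would not undo the shared group, would not make the sham match in everything visible, and would not add raters to the check described.

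**Adverse events go to a coordinator.** Section 2.14 says so, and no section has PASI raters take the adverse-event history. Shared weeks do not prove shared staff. This stands. The open part is what happens at the visit itself, where raters also look at skin in the treated regions.

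**Most reactions are not arm-specific.** The same needle enters muscle in both arms, so pain, redness and bruising can occur in both, and induration is not assigned to either. This stands; only expulsion is strictly suture-specific.

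**The group is for adherence.** True, and no section says that participants post symptoms there. But nothing stated stops them.

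**Stronger readings that the document does not support.** A reader might infer that the blinding fails. The text shows a route, with no reaction rate and no evidence that the route is used. A reader might also size the bias from a bad case: 40% unmasked × 0.5 points = 0.20 PASI points, against 0.35 × 1.5 = 0.525 points for an assumed baseline of 1.5, or 38%. None of the 40%, the 0.5 or the 1.5 is in the article. The 0.35 is a difference in responder proportions, not a mean improvement. PASI is also averaged over two raters, so the full shift needs both to be unmasked and equally swayed.

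**Conclusion.** The point holds in a limited form. Blinding of raters and participants is not secured against suture-only signs, so the guarantee in Section 2.2 and the claim of complete visible and sensory match in Section 2.3 go further than the article's own content allows. This rests on four stated facts: foreseen suture expulsion, PASI and adverse events at the same visits, one chat group for both arms, and a blinding check without the raters.

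The size is undetermined. Under the assumptions above it runs from negligible (false-positive rate within about 2 percentage points of nominal at 10% unmasked) to serious (up to 34.8% on the responder scale at 50% unmasked with the largest shift). It applies to PASI, BSA, PGA, DLQI and itch. BMI, the measured co-primary, is much less exposed. This should be corrected because the remedy is cheap, not because a failure of blinding has been shown.

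**What to change.** 1. Replace the shared WeChat group with individual chats or a one-way broadcast channel.
2. At each visit, score PASI, BSA and PGA before any adverse-event history is taken. Have the coordinator named in Section 2.14 take the reports and inspect the sites afterwards. Keep adverse-event records from the raters until week-8 data are locked, and ask participants not to discuss the sites with them.
3. Add the outcome raters to the blinding assessment and carry it out at week 8.
4. Soften the wording in Sections 2.2 and 2.3, and name this route in Section 4.

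If the full protocol already contains item 2, a sentence in the article is enough.

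I would not cover the treated sites with dressings. With eligibility at PASI < 3 or BSA < 3%, 14 dressings could hide plaques that should be scored and add error to a co-primary endpoint.

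Cost: slightly more visit logistics and the loss of peer interaction in the group. No extra staff are needed, and the sample size stays at 35 per arm.

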### Rationale for the sham control

2.3

A sham procedure was selected as the control for the following reasons:

(1) *Methodological rigor*: As a double-blind, randomized controlled trial, a sham procedure is essential. It matches the verum ACE in all visible and sensory aspects, ensuring effective participant blinding and controlling for non-specific effects (e.g., placebo, natural disease variation). This allows for an objective assessment of the specific therapeutic efficacy attributable to the catgut embedding.(2) *Establishing clinical superiority*: Current standard treatments for mild psoriasis have limitations, including side effects and lack of efficacy for obesity. This trial aims to prove that ACE offers a specific therapeutic benefit, which necessitates comparison against a non-active intervention is necessary to establish its distinct clinical value and therapeutic advantage.

### Research objectives

2.4

*Primary objective*: to evaluate the efficacy of ACE therapy as an adjunctive treatment for improving the PASI score and reducing BMI after 8 weeks in patients with mild psoriasis and overweight.*Secondary objectives*: (1) to assess the changes in secondary efficacy indicators of psoriasis, BMI, waist circumference (WC), WHR and metabolic-related indicators, etc. measures from baseline to week 8. (2) to document the incidence of adverse events (AEs) throughout the study period. (3) to determine the psoriasis recurrence rate during the follow-up period.

### Inclusion criteria

2.5

(1) Aged 18 years or older, male or female.(2) Clinical diagnosis of plaque psoriasis with blood stasis syndrome confirmed by traditional Chinese medicine criteria.(3) Mild psoriasis, defined as PASI score < 3 or BSA < 3%.(4) Overweight, defined as BMI ≥ 24 kg/m^2^.(5) Ability to comprehend the study objectives, procedures, potential benefits, and risks.(6) Willingness to complete all scheduled visits and provide truthful feedback.(7) Provision of voluntarily signed informed consent.

